# Physiotherapeutic scoliosis-specific exercises performed immediately after spinal manipulative therapy for the treatment of mild adolescent idiopathic scoliosis: study protocol for a randomized controlled pilot trial

**DOI:** 10.1186/s13063-020-05000-y

**Published:** 2021-01-14

**Keywords:** Spinal manipulative therapy, Physical exercise, Adolescent idiopathic scoliosis, Somatosensory evoked potentials

## Abstract

**Background:**

Spinal manipulative therapy is commonly used in the treatment of adolescent idiopathic scoliosis. Some therapists also rely on physiotherapeutic scoliosis-specific exercise (PSSE). Combining these two modalities seems reasonable, but the effectiveness of this combination has never been rigorously tested. Here, a protocol for a pilot study is proposed to determine the feasibility of conducting a larger randomized trial. The pilot study was designed to test the hypothesis that spinal manipulative therapy followed by PSSE is more effective than PSSE alone in improving the Cobb angle, sensorimotor integration, the angle of trunk rotation (ATR), body symmetry, and quality of life.

**Methods:**

The protocol describes a randomized controlled pilot trial with 40 subjects divided into study and control groups. Both groups will receive 8 weeks of PSSE, but the study group will also receive spinal manipulative therapy during the first 2 weeks before PSSE. The primary outcome will be an estimate of the feasibility of conducting a full-scale experiment. The influencing factors will be the time to complete enrollment, the recruitment rate, subject retention, and adherence to the treatment allocations. The secondary outcomes that will be used to assess the efficacy of treatment will include the Cobb angle, somatosensory evoked potentials, ATR, three-dimensional postural parameters, and scores on the 22-item Scoliosis Research Society outcomes questionnaire. The Cobb angle will be measured at baseline and at the end of 8 weeks of training. The somatosensory evoked potentials will be measured at baseline and at the end of 2 weeks of training. The ATR, three-dimensional postural parameters, and scores on the 22-item Scoliosis Research Society outcomes questionnaire will be measured at baseline and at 2 weeks, 4 weeks, and 8 weeks of treatment.

**Discussion:**

This study will inform the design of a future full-scale trial. The outcomes will provide preliminary data about the efficacy of the combination of spinal manipulative therapy and exercise in treating scoliosis.

**Trial registration:**

Prospectively registered at Chinese clinical trial registry, ChiCTR1900027037. Registered on 29 October 2019.

http://www.chictr.org.cn/edit.aspx?pid=44954&htm=4

**Supplementary Information:**

The online version contains supplementary material available at 10.1186/s13063-020-05000-y.

## Background

Adolescent idiopathic scoliosis (AIS) is characterized by structural, lateral, and rotated curvature(s) of the spine in individuals aged 10–18 years old, and AIS accounts for 70–80% of the scoliosis cases [1, 2]. The reported incidence of AIS in China is approximately 2.4–5.1% [3, 4]. Its etiology remains unclear [5, 6]. Importantly, AIS is very progressive. As the degree of scoliosis increases, it may cause back pain, psychological problems, cardiopulmonary dysfunction, and other issues, severely affecting the physical and mental health of teenagers [7–10]. The prevalence of back pain has been reported to range from 22.5 to 68% [7, 11]. Recent studies have found that AIS patients are more prone to not only musculoskeletal problems but also problems of balance, sensorimotor control, sensorimotor integration, and motor control than are normal subjects [12–15].

Many nonsurgical treatments have been proposed to delay the need for surgery, with the goal of preventing or reversing the progression of the spinal curvature, but few of these treatments have been included in the guidelines recently published by the International Scientific Society of Scoliosis Orthopedic and Rehabilitation Treatment (SOSORT) [1]. Braces and physiotherapeutic scoliosis-specific exercises (PSSE) are the only two treatments supported by level I evidence and accepted by the SOSORT. Due to the physical discomfort of wearing a brace and the psychological distress resulting from its appearance [16–18], braces are recommended only for growing patients with progressive idiopathic scoliosis exceeding 25°. PSSE, however, is recommended as the first choice for mild AIS (Cobb angle < 25°) to halt the progression of the deformity [1]. Simultaneous, active, three-dimensional PSSE for correction is emphasized to improve sensorimotor integration and motor control [19].

Spinal manipulative therapy (SMT) is commonly used to treat musculoskeletal dysfunction. It has a significant curative effect on pain, flexibility, and mobility [20–22]. However, it has not yet been shown to be effective in treating AIS. Contradictory research results have been reported, and the research has often been of poor quality. Reports of SMT reducing the Cobb angle and trunk rotation have often been included in case reports or pre-and-post studies [23, 24]. One randomized controlled trial (RCT) showed that manual therapy did not affect trunk morphology or spine flexibility. However, in that RCT, the patients received manual therapy without PSSE [25]. Another pilot RCT confirmed the feasibility of performing RCTs on manipulation for scoliosis and compared chiropractic care with standard medical care [26]. There is a great need for high-quality RCTs to verify the efficacy of manual therapy in treating AIS.

Interestingly, there is evidence that high-velocity, low-amplitude (HVLA) spinal manipulation can induce cortical plasticity which improves sensorimotor integration and alters motor control [27]. Changes in motor evoked potentials [28] and sensory evoked potentials [29] as well as changes in the amplitude of maximum voluntary contractions [30] have been observed after HVLA manipulation. Together, these observations together suggest that HVLA manipulation alters somatosensory processing [31] and improves motor performance for at least 60 min after a typical HVLA manipulation session [32]. Thus, we hypothesize that active PSSE during the period of improved sensory-motor integration after SMT might thereby improve the training effect and lead to better a posture and quality of life.

A randomized and controlled pilot trial was therefore designed to test this idea. The pilot trial will investigate the feasibility of conducting RCTs on this topic with regard to recruitment (e.g., time to complete enrollment, recruitment rate), subject compliance with the study protocols, and adverse events. A secondary aim is to investigate the effect size of SMT combined with PSSE by comparing a group receiving SMT with PSSE and a group receiving PSSE only. The outcomes are the Cobb angle, somatosensory evoked potentials (SEP), the angle of trunk rotation (ATR), three-dimensional postural parameters (3-DPPs), and the 22-item Scoliosis Research Society outcomes questionnaire (SRS-22) score.

## Methods/design

### Study design

The study will be a nonblinded pilot RCT with two parallel groups. The protocol will follow the Declaration of Helsinki and will be conducted according to the standard protocol items: recommendations for interventional trials (SPIRIT) guidelines and the World Health Organization trial registration data set (version 1.2.1) guidelines for clinical trial protocols (see Additional file 1 and Additional file 2). It will be conducted in the Rehabilitation Department of Tongji Hospital at Huazhong University of Science and Technology in Wuhan, China. AIS subjects will be recruited from the hospital’s outpatient rehabilitation department. To recruit more subjects, we will post study-related advertisements in the Outpatient department and WeChat app. A flow diagram is shown in Fig. 1.

**Fig. 1 Fig1:**
[figure not shown]
The flow diagram for this trial

### Eligibility

The inclusion criteria will be as follows [33]:
Age of 10–18 years.A diagnosis of idiopathic scoliosis.Cobb angle of 10–25°.Risser sign of 0–2.Agree not to receive any other treatments for scoliosis such as brace and insoles during the study period.

The exclusion criteria will be as follows:
Contraindications for exercise, such as cardiovascular or respiratory insufficiency.Contraindications for SMT, including inflammation, infection, advanced degeneration, congenital malformations, trauma, and cerebrovascular anomalies [34].A history of spinal surgery.A history of scoliosis treatment involving surgery, a brace, exercise, etc.

In addition to the simple unwillingness to continue, factors that can prevent a subject from continuing to participate, such as a new diagnosis of a severe disease, will be considered valid grounds for withdrawal.

### Randomization and blinding

The physician will explain the whole content of the trial to the candidates who meet the eligibility criteria in a separate room. Written informed consent from both subject and their statutory guardians are required. Their demographic information and medical history will then be recorded.

Each subject will be assigned to either the study or the control group using simple randomization with a 1:1 allocation. The random sequence will be generated by an investigator using an electronic random sequence generator (www.random.org). The numbers in the random sequence will be sealed in consecutively numbered, opaque envelopes. When required, the envelopes will be opened by a person who will not be involved in the intervention, assessment, or statistical analysis.

Due to the nature of the interventions, blinding of the therapists and subjects to the intervention type will be impossible, so only the assessors and those performing the statistical analysis be blinded to the allocation results. To ensure that the group allocation results remain concealed as much as possible, the assessors will process the assessments in a separate room, and the statistical analysis will not include the information about the subjects and their allocations. The schedule for the treatments and outcome assessments is presented in Fig. 2.

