### Sample size

G*Power 3.1.9.7 was used to execute the power calculations. The change of the Cobb angle was chosen as the primary outcome indicator. Referring to the two studies from Zheng (*d* = 0.8) [59] and Liang et al. (*d* = 1.2) [60], we set the value of effect size *d* = 1.0 in our study. With a significance level of 5%, 17 subjects are needed in each group to reach a power of 80%. Allowing for a dropout rate of 15%, a total of 40 subjects will be recruited with 20 subjects for each.

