### Data collection, data management, and statistical analysis

The primary outcome measures will be tabulated and interpreted with respect to the goals established a priori.

To estimate the sample size required for a future full-scale RCT, between-group effect sizes and their 95% confidence intervals will be calculated by applying Hedges’ correction. A minimum power of 80% will be used to detect changes in the Cobb angles, ATRs, 3-DPPs and SRS-22 scores (*α* = 0.05). The sample size will be increased to allow for an estimated 20% dropout rate. Statistical methods for the secondary outcome measures will be evaluated via comparisons of changes between groups.

The data will be double entered into EpiData 3.1 software (The EpiData Association, Odense, Denmark) and then transferred to version 22.0 of the SPSS software suite (IBM, Armonk, NY, USA) for the analyses. The threshold for significance will be taken as *α* ≤ 0.05. A statistician who will be blinded to the allocation results will analyze all the data. The continuous variables will be presented as means ± SDs, and the categorical variables will be presented as ratios. The baseline readings will be compared using independent samples *t* tests or chi-squared tests. For the Cobb angles and SRS-22 scores, independent samples *t* tests will be used to compare the two groups, and paired *t* tests will be used for within-group comparisons. For the M, U, MU, and M+U SEP peak amplitudes and latencies, nonparametric Wilcoxon signed-ranks tests will be used to compare these values between and within the groups. For the 3-DPPs and ATR, repeated measured analysis of variance will be used for the between-groups and within-groups comparison. Furthermore, we will perform subgroup analysis by age group (age < 13 years and age ≥ 13 years) [2, 33]. To deal with the missing data, a sensitivity analysis and weighted estimating equations will be used as the primary approach [61].

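### Simple randomization of 40 subjects seldom gives the stated 20 per group and leaves balance on the planned age groups to chance; the power cost is small

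*Protocol article*

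**What the plan says.** Under Randomization and blinding, the protocol article allocates each subject "using simple randomization with a 1:1 allocation". It adds: "The random sequence will be generated by an investigator using an electronic random sequence generator". The numbers go into sealed, numbered, opaque envelopes. No blocks, strata, minimization or cap on arm size is named.

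Under Sample size, the basis is the change in Cobb angle: "we set the value of effect size *d* = 1.0 in our study". At the 5% level this leads to 17 evaluable per group for 80% power. Then: "Allowing for a dropout rate of 15%, a total of 40 subjects will be recruited with 20 subjects for each".

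Under Data collection, data management, and statistical analysis, the Cobb angle is compared between groups by an independent-samples t test with no covariate named. The same section states: "we will perform subgroup analysis by age group (age < 13 years and age ≥ 13 years" (the cut is at 13 years). Eligibility admits ages 10 to 18, so the cut lies inside the recruited range.

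**The concern.** The sample-size section treats 20 per group as what the trial will have, but the stated allocation method does not produce it. Coin-toss allocation gives random arm sizes, and unequal arms have less power than equal arms of the same total.

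The second part concerns age. The plan treats the cut at 13 as important enough for a subgroup analysis, yet neither the allocation nor the stated Cobb analysis takes account of it. With 40 subjects, the arms may end with visibly different age mixes, and a subgroup may have very few subjects in one arm. This bears on the pilot's purpose, because its between-group effect sizes are to guide the choice of the full trial's primary outcome and its sample size.

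**Working it through.** **Inputs.** Sample size section: d = 1.0, alpha 5% (taken as two-sided, which reproduces the stated 17), power 80%, 17 evaluable and 20 recruited per group, dropout 15%. Randomization section: simple, 1:1. Analysis section: age cut at 13. The share aged under 13 is not given and is assumed below.

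**1. The plan's own figure.** Power of the two-sample t test is P(|T| > t(0.975; n1+n2−2)), where T is noncentral t with n1+n2−2 degrees of freedom and noncentrality d·√(n1·n2/(n1+n2)).
- 16:16 gives 78.1%.
- 17:17 has noncentrality √(289/34) = 2.915 and gives 80.7%. So 17 is right.
- Dropout: 17/(1 − 0.15) = 20 per group, 40 in total. This is also right.

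**2. Arm sizes under simple randomization.** The size of one arm is Binomial(40, 0.5).
- P(20:20) = C(40,20)/2^40 = 12.5%.
- P(22:18 or worse) = 63.6%.
- P(24:16 or worse) = 26.8%. The smaller arm is then below 17 before any dropout.
- P(26:14 or worse) = 8.1%.
- Expected difference between arms: 5.0 subjects.

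**3. Power at the resulting splits.** With 40 × 0.85 = 34 evaluable and d = 1.0:

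| Split of 34 | Power |
|---|---|
| 17:17 | 80.7% |
| 18:16 | 80.6% |
| 19:15 | 80.2% |
| 20:14 | 79.5% |
| 21:13 | 78.5% |
| 22:12 | 77.1% |

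The average over Binomial(34, 0.5) splits is 79.5%. The loss against balance is 80.7 − 79.5 = 1.2 percentage points.

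**4. Age balance under simple randomization.** Suppose exactly 20 of the 40 are aged 13 or over. Let X be the older and Y the younger subjects in the study arm, each Binomial(20, 0.5). The difference in the share aged 13 or over is |X/(X+Y) − (20−X)/(40−X−Y)|. Summing exactly, it is at least 0.20 with probability 26.8%.

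Other assumptions about the share give:
- exactly 16 of 40 under 13: 22.6%;
- exactly 12 of 40 under 13: 18.7%;
- each subject independently under 13 with probability 0.3 to 0.5: 18% to 22%.

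The range is therefore about 18% to 27%. The younger group is split 2:1 or worse in 39% of sequences if it has 12 subjects, 21% if 16, and 12% if 20.

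**5. Blocking without stratification does not help age.** With exactly 20:20 and 20 of 40 aged 13 or over, the hypergeometric chance of a difference of 20 points or more is 34.3%. Part of this is granularity, since 12 against 8 is exactly 20 points. Balance on age needs stratification, minimization or adjustment.

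**6. What an imbalance does to the estimate.** If age group shifts Cobb change by δ, a 20-point imbalance shifts the unadjusted group difference by 0.20·δ, in either direction with equal chance. The documents give no value for δ.

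**The case against.** Much can be said for the plan as written. Simple randomization is valid, and its chance imbalances are already allowed for in the t test's error rate. In an open trial at one centre it keeps the next allocation unpredictable, which is a defensible reason to choose it. The stated primary outcome is feasibility. The 20 per group can be read as the expected number under 1:1 allocation. A planned subgroup analysis does not require stratified randomization, and the Risser 0–2 criterion already narrows skeletal maturity. All of this stands, and it limits the weight of the point.

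A reader might infer that the trial is underpowered because many splits fall below 80%. That does not follow. The plan clears 80% by only 0.7 points, so small departures cross the line. With exactly 20:20 and independent 15% dropout, power is still below 80% in about 40% of realizations (average 80.3%); with simple randomization and the same dropout it is about 51% (average 79.3%). Uncertainty about d, set at 1.0 between cited values of 0.8 and 1.2, matters far more than one point of power.

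A reader might also infer that age confounds the comparison. The documents do not support that: allocation is random, so any imbalance is chance, and no effect of age on 8-week Cobb change is given.

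The objection does not remove the mismatch between the two sections. If the envelopes in fact hold a fixed list of 20 and 20, the description as simple randomization is what needs correcting.

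**Conclusion.** The point holds, at modest weight. The stated 20 per group does not follow from the stated allocation method: about seven sequences in eight miss it, and about one in four gives 24:16 or worse. The average power loss is about 1.2 points, assuming d = 1.0, a two-sided 5% test and 34 evaluable subjects. The calculation of 17 and then 20 per group is itself correct.

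The better reason to act is age. With half the subjects aged 13 or over (assumed), a difference of 20 points or more between arms occurs about 27% of the time, and 18% to 27% over the assumptions shown. The unadjusted test does not absorb it. This may leave chance imbalance and reduce the precision of the effect size carried into the full trial; it does not bias the comparison. How much precision is lost depends on how strongly age relates to Cobb change, which the documents do not say.

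**What to change.** 1. Include age group (under 13, 13 and over) as a covariate in the between-group analysis of Cobb change. Age is already recorded at baseline, so this costs one model term and helps whatever allocations have already been made.
2. For the remaining allocations, use permuted blocks of varied sizes, not disclosed to recruiting staff or therapists, stratified by age group and kept in the same kind of sealed envelopes. This needs a new sequence and two sets of envelopes, and no extra subjects. The downside is slight predictability in an open single-centre trial, limited by the varied, concealed block sizes. Exact 20:20 is not guaranteed, because earlier imbalance remains and the last block in a stratum may be incomplete.
3. Reconcile the Sample size and Randomization and blinding sections. If simple randomization is kept, state about 20 per group and power of about 79–80%.

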**Fig. 2 Fig2:**
[figure not shown]
Schedule of enrolment, interventions, and assessments throughout the trial. PSSE, physiotherapeutic scoliosis-specific exercise; SEP, somatosensory evoked potentials; ATR, angle of trunk rotation; 3-DPPs, three-dimensional postural parameters; SRS-22, the 22–item Scoliosis Research Society Outcomes Questionnaire

### Intervention

#### Physiotherapeutic scoliosis-specific exercises

Each subject will undergo outpatient PSSE under the supervision of therapists during 30 min sessions, 5 times per week, for 4 weeks; then, they will undergo another 4-week home-based PSSE regimen implemented under the supervision of their parents, with 30-min sessions performed 5 times a week. The PSSE will include autocorrection in three dimensions, stabilization of the corrected posture, training related to activities of daily living and patient education [35]. The PSSE program will be developed based on the work of Schroth [36, 37] and on the scientific exercise approach to scoliosis [38]. Three-dimensional active correction involves correcting the curvature in the coronal plane, rotation in the horizontal plane, and abnormal physiological curvature in the sagittal plane at the same time. During training, the individuals gradually transition from lying to sitting, and finally to standing. A balance pad or wedge pad will be used for correcting the lateral curvature or hump, and an elastic band will be used to help stabilize the subjects in the corrected posture. Rotational breathing will be involved to correct vertebral rotation as well as asymmetry in the thorax [19]. The subjects will be trained to draw in air to the concave side when inhaling and to expel air first from the convex side when exhaling. At the beginning, the therapists will use their hands to guide the subjects to inhale or exhale correctly. As the subjects become more skilled, breathing under supervision will continue to be required. Meanwhile, the therapists will instruct the subjects on how to integrate their exercises into their daily activities, such as standing and sitting. It will also be necessary to educate the subjects and their parents about the types of scoliosis, possible hazards, and the risk of progression. The PSSE will be guided by two therapists with more than 4 years of experience in the treatment of scoliosis. Some PSSE examples are shown in Fig. 3.

**Fig. 3 Fig3:**
[figure not shown]
Physiotherapeutic scoliosis-specific exercises. **a** Education about good sitting position. **b** The plank position during standing, with both shoulders abducted and externally rotated. **c** Rotary breathing training in squatting. **d**–**f** Active 3-dimensional correction in front of a mirror while the individual is seated

#### Spinal manipulative therapy

In the first 2 weeks, the study group will additionally receive SMT before PSSE 5 times a week. SMT will involve 5 min of evaluation, 10 min of soft tissue relaxation techniques, and 15 min of HVLA manipulation.

Before SMT is performed, it is necessary to evaluate and find the dysfunctional spine segments. Pain and tenderness during palpation or the examination of local tissue are the primary indicators used for identifying the dysfunctional segments [39]. Restricted joint mobility during the spinal examination is also an important indicator [39]. In this study, if the physiotherapist finds any pain, tenderness, or restricted joint mobility when assessing the region from C7 to S1 and the sacroiliac joints, the segments involved will be defined as dysfunctional and recorded as target segments for treatment. For thoracic and lumbar segments, the alignment of the spinous processes is assessed with unilateral or bilateral fingertip contacts. Any potential tenderness or pain around the spinous processes and soft tissues will be recorded. In addition, coupled lateral flexion and rotation movements will be induced on both sides in the extended and flexed positions. For example, the examiner will stand on the subject’s left side, place his right thumb on the right thoracic spinous process, and guide the subject’s upper body with his left hand from a neutral and upright sitting position into rotation and lateral flexion position until the movement reaches the palpating thumb. During the examination, if the subject complains of pain or the examiner observes asymmetric motion between the left and right sides, that means the segments are dysfunctional. For the sacroiliac segments, the subjects will stand barefoot on a firm surface, and the therapist will first palpate the posterior superior iliac spine on both sides and assess the asymmetry as well as the presence of any pain or tenderness during palpation. The positions of the bilateral sacroiliac joint surface projections will be assessed at the same time. The evaluation procedure will be based on that described in chapters 9 to 11 of the palpation techniques book: surface anatomy for physical therapists [40].

After the examination of all segments is completed, the therapist will perform 10 min of soft tissue relaxation on the dysfunctional segments by using rolling manipulation, a form of traditional Chinese massage. The subjects will be instructed by the therapist to lie in the prone position and to relax their mind and body. The therapist will contact the treatment site with the dorsal side of his fifth metacarpophalangeal joints and then sink the shoulders and loosen the wrists, with the elbow joint serving as the support. The forearm will actively swing, driving flexion and extension of the wrist joint and rotation of the forearm. The metacarpophalangeal joints will be rolled back and forth on the treatment site at a frequency of 120–160 times/min [41].

After soft tissue relaxation, the therapist will perform HVLA manipulation on the dysfunctional segments to address the subject’s pain, muscle tension, and limited segmental activity. Figure 4 outlines the main HVLA manipulation procedures in our research. For example, Fig. 4c outlines the HVLA technique for adjusting the extension of middle thoracic section. To induce extension with the patient in the supine patient position, the thenar contacts are typically established over the transverse processes of the inferior vertebral segments. The joint to be adjusted is bent into extension over the top of the posterior contact, and the therapist exerts a force posteriorly, using body weight to induce distraction in the joints above the contact. All HVLA manipulation methods will be based on that described in chapter 5 of the chiropractic technique book [42]. The treatment will be stopped immediately if discomfort occurs. One physiotherapist with 10 years of HVLA manipulation experience will perform all the examinations and manipulations.

